|                       | 
 
▪ All AEs
 
▪ Serious AEs
 
▪ Serious AEs related to Eurartesim® treatment
 
▪ AEs of special interest (AESIs)
 
▪ AEs which caused early discontinuation of Eurartesim®
 
▪ AEs related to Eurartesim® treatment
 
 
Specific analyses will be carried out on the AESIs. Correlation analyses will be carried out in order to verify if their occurrence is more frequent with the previous/concomitant use of other drugs (specific classes to be determined in the statistical analysis plan), including antimalarials, in presence of co-morbidity (specific classes to be determined in the statistical analysis plan), or in presence of parasitaemia.
 
Compliance will be computed in the whole population and in the subset of 1,000 patients, calculating for each patient the ratio between the number of tablets taken and the number of tablets that the patient should have taken. Two groups of patients shall be described: compliant = 100% treatment compliance and non-compliant = other cases. The safety profile of compliant vs non-compliant patients will be compared.
 
Additional analysis in the sub-set population
 
QTc data will be recorded and analysed according to the method described in the ICH guideline E14. The impact of all recorded covariates on QTc prolongation will be investigated through analysis of covariance techniques.
 
For the AESIs possibly related to cardio-toxicity, a correlation analysis with QTc values recorded at the visit of Day 3 (both before and 3-4 hour after treatment administration) will be carried out. Occurrence of these events will also be studied with respect to distance from food intake.
 
Laboratory values will be analysed after normalization. Shift tables from normal to abnormal and vice-versa will be generated.
 
All the analyses previously described will be also performed by class of age and by type of Plasmodium.
 |

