If the results are abnormal, the blood examination will be repeated until normalization. Triplicate ECG and blood sampling for PQ concentration assessments (in all the 1,000 patient subgroup) will be performed on Day 1 (before drug administration); single ECG and blood sampling for PQ concentration (in all the 1,000 patient subgroup) will be repeated on Day 3, before the last dose of Eurartesim® and 3 to 4 hours after the last drug administration (in this latter case ECG will be performed in triplicate), as well as on Day 7; safety information will be collected at all these visits. **Each PK sample will be 2 mL of whole blood which makes a total of 8 mls for the entire study period unless clinically indicated.**

If the QTcF (QT corrected by Fridericia's formula) value assessed on Day 3 before last dose is above 500 ms, Eurartesim® should be withheld until QTcF returns below 480 ms within 6 hours. Thereafter, the Eurartesim® cycle may be completed under frequent QTc monitoring based on medical judgment. If the QTcF should not return below 480 ms within 6 hours, another antimalarial therapy should be considered.

The occurrence of any adverse events will be solicited from the subset of **about 1,000** patients on Days 3 and 7 following administration of Eurartesim® as well as in any additional visits.

All patients in the study with a cardiac event of special interest (see section 8.5) will have an ECG performed.

Patients will be asked to report to the health facility or to the HDSS if any adverse event occurs after Day 5 ( $\pm$  2 days) contact and within 28 days after the start of Eurartesim® intake.

Female patients will be encouraged to communicate to the study team if they get pregnant within a period of two months after the start of the Eurartesim® treatment. In these cases, information on the evolution of the pregnancy will be collected at 3, 6, 9 months and after the delivery (6 and 14 weeks). Information on the drugs taken during the pregnancy as well as AEs/SAEs/AESIs and the health status of the newborn/s will be collected.

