To facilitate drug administration in small children, tablets will be crushed on a spoon and given with water. If vomiting occurs within 30 min from drug administration, dose will be re-administered. If vomiting occurs within 30 to 60 min, half a dose have to be re-administered. Re-dosing should not be attempted more than once. The first study drug administration will be supervised at the site in all the patients, instruction on the second and the third drug administration will be given to patients.

In the nested 1000 patient group, the second administration will be given preferably at the study site or at the patient's home by a trained CHA. If the dose is administered at home, a specific diary will be provided to the patient in which the CHA have to fill in the second drug administration data. This diary will be maintained by the patient and will be returned to the site when the third administration will be provided (at the site).

Eurartesim® will be provided free of charge by Sigma-Tau ifr S.p.A.

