#### **7.3.2 Premature treatment discontinuation**

The reasons of any premature treatment discontinuation will be collected by the CHA or HF staff during his/her visits/contacts and in case the reason to stop the treatment is the occurrence of an adverse event, this will be described on the specific section of the patient chart and treated depending on its category (see section 8).

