### **9.2 Analysis in the whole sample**

#### **Analysis in the whole sample and in the Subset population**

The statistical analysis will be mainly descriptive. The estimates of the incidence of adverse events will be based on crude rates. All estimates will be complemented with appropriate 95% confidence intervals.

The adverse events shall be regularly coded using MedDRA before database lock.

All SAEs and AESIs will be reviewed centrally by an independent safety monitoring panel.

Incidences will be computed on the following classes of AEs, overall and by SOC/PT:

- All AEs
- Serious AEs
- Serious AEs related to study treatment
- AEs of special interest (AESIs)
- AEs which caused early discontinuation of Eurartesim®
- AEs related to Eurartesim® treatment

Specific analyses will be carried-out on the AESIs. Correlation analyses will be carried-out in order to verify if their occurrence is more frequent with the previous/concomitant use of other drugs (specific classes to be determined in the statistical analysis plan), including antimalarials, in presence of co-morbidity (specific classes to be determined in the statistical analysis plan), or in presence of parasitaemia.

Compliance will be computed in the whole population and in the subset of **about 1,000** patients, calculating for each patient the ratio between the number of tablets taken and the number of tablets that the patient should have taken. Two groups of patients shall be described: compliant = 100% treatment compliance and non compliant = other cases. The safety profile of compliant vs non-compliant patients will be compared.

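### The compliant versus non-compliant safety comparison does not separate patients whose adverse event itself ended treatment, so adverse events partly define the groups being compared

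*Protocol*

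**What the plan says.** Section 9.2 of the protocol computes compliance in the whole population and in the nested subset by "calculating for each patient the ratio between the number of tablets taken and the number of tablets that the patient should have taken". It then forms two groups and commits to comparing them: "compliant = 100% treatment compliance and non compliant = other cases. The safety profile of compliant vs non-compliant patients will be compared". The Statistical analysis entry of the Section 1 summary repeats this: "The safety profile of compliant vs non-compliant patients will be compared".

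Other sections bear on who falls into which group:

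- Section 7.3.2 has the reasons for premature discontinuation collected and provides for the case "in case the reason to stop the treatment is the occurrence of an adverse event".
- Section 9.2 lists "AEs which caused early discontinuation of Eurartesim" among the AE classes for which incidences are computed.
- Section 5.1 says that, in the nested subset, if QTcF before the last dose is above 500 ms, treatment "should be withheld until QTcF returns below 480 ms within 6 hours". The course may then be completed; if QTcF does not recover in that time, another antimalarial should be considered.
- Section 5.3 instructs re-dosing after early vomiting, including a partial re-dose: "If vomiting occurs within 30 to 60 min, half a dose have to be re-administered".
- Section 8.4 records AEs from the signing of consent, so the three dosing days are inside the window.
- Section 7.2.3 collects the number of tablets not taken, the reason, and the date each event first appeared.

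**The concern.** Compliance is only known once the course has ended, and an AE during the course can determine it. When an AE makes the patient stop, that one event counts as an outcome and also assigns the patient to the non-compliant group. The groups then differ in AE frequency by construction, whatever the effect of taking or missing tablets.

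The clearest sign is the class of AEs that caused early discontinuation. It can have essentially no cases among patients who took every tablet, so its imbalance says nothing about adherence. In the nested subset a QT finding that prevents the third dose acts the same way.

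The dosing days carry much of the information. In the main group the only solicited contact is at Day 5 (± 2 days), and it asks about events since the inclusion visit; later events depend on spontaneous or hospital reports. A reader of the report could take the resulting contrast as evidence that full adherence protects against AEs. Section 9.2 leaves drug and co-morbidity classes to the SAP, but it fixes this grouping and this comparison itself.

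**Working it through.** The protocol states no figure for this comparison, so there is none to reproduce. The check has two parts.

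**1. Who is classed as non-compliant**

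Take the 36 to <75 kg band in Section 5.3: 3 tablets × 3 days = 9 tablets due.

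- Stops before the third dose because of an AE: 6/9 = 67%, non-compliant because of the AE.
- Third dose never given because of QTcF: 6/9 = 67%, non-compliant because of the QTcF finding.
- Third dose delayed by QTcF, then taken: 9/9 = 100%, compliant.
- One full re-dose after vomiting: 12/9 = 133% if the replacement counts only as taken; 12/12 = 100% if it also counts as due; (9 − 0)/9 = 100% if compliance is worked out from tablets not taken. Section 9.2 does not say which applies.

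The first two cases follow from the stated rule. The last is open.

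**2. Size of the artefact when compliance has no effect**

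Inputs, all assumed because the protocol gives none:

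- p = risk of an AE before the last dose
- q = non-compliance unrelated to AEs
- s = share of AE patients who stop because of the AE

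Formulas:

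- AE risk, non-compliant = [q·p + (1 − q)·p·s] / [q + (1 − q)·p·s]
- AE risk, compliant = p·(1 − s) / (1 − p·s)

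With p = 0.10, q = 0.05, s = 0.05:

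- Non-compliant: (0.005 + 0.00475) / (0.05 + 0.00475) = 0.00975/0.05475 = 17.8%
- Compliant: 0.095/0.995 = 9.5%
- Risk ratio 1.87

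With s = 0.10:

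- Non-compliant: (0.005 + 0.0095) / (0.05 + 0.0095) = 0.0145/0.0595 = 24.4%
- Compliant: 0.09/0.99 = 9.1%
- Risk ratio 2.68

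Over p = 5% to 20%, q = 2% to 10% and s = 2% to 10%, the ratio runs from 1.16 (p = 20%, q = 10%, s = 2%) to 5.24 (p = 5%, q = 2%, s = 10%). It is largest when unrelated non-compliance is rare.

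The 95% confidence intervals promised in Section 9.2 would not expose the problem. With 10,000 patients and s = 0.10, there are 595 non-compliant patients. Their interval is 24.4% ± 1.96 × √(0.244 × 0.756/595), about 20.9% to 27.8%. For the 9,405 compliant patients it is about 8.5% to 9.7%. The intervals are far apart although compliance does nothing.

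If every patient stopped by an AE is moved to a third category, the AE risk in both remaining groups is p·(1 − s)/(1 − p·s), and the ratio is 1.

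**The case against.** The strongest defence is that the analysis is described as mainly descriptive, is not the primary estimate, and comes with no named test or causal claim. AEs leading to discontinuation are tabulated as their own class, the reasons for stopping are collected, and time-ordering is often SAP material. This limits the consequence. It does not remove the point: the protocol itself fixes the two groups and the comparison, and does not use the collected reasons in forming them.

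A reader might also infer more than the documents support:

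- **That re-dosing after vomiting makes a patient non-compliant by definition.** Section 7.2.3 records tablets not taken, and the summary's Evaluation criteria count tablets dispensed but not taken in the nested subset. A ratio built on those counts cannot exceed 100%. The re-dose is also instructed, so it can be read as part of what should have been taken. What remains is an ambiguity in Section 9.2.
- **That any withheld third dose means non-compliance.** Section 5.1 allows the course to be completed after QTcF recovers. Only patients who never receive the dose are affected. Section 3.2 reports no healthy subject above 500 ms; these are not patient data, but nothing in the protocol suggests that this route is common.
- **That non-compliance in the nested subset is almost only event-driven.** Its dosing is largely supervised, but a missed home visit or Day 3 attendance is another cause, and no figure is given.
- **That the comparison is certain to show more AEs in non-compliant patients.** Only events before the last dose can drive the grouping, while AEs are captured to Day 28. Less exposure after stopping could lower later AEs, so the net direction is not fixed.

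**Conclusion.** The point stands for patients whose AE, or in the nested subset whose QTcF, ended the course. The stated grouping puts them in the non-compliant group because of the event, and dosing-period AEs are over-represented there even when compliance has no effect.

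Under the assumed 10% AE risk, 5% unrelated non-compliance and 5% to 10% of AE patients stopping, the spurious risk ratio is about 1.9 to 2.7. This illustrates the mechanism and is not a forecast for this study: every input is assumed, and the model covers only AEs before the last dose. It should be corrected because the comparison as written cannot be interpreted. It does not touch the primary crude incidences. Re-dosing after vomiting is a separate, smaller matter of unclear counting.

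**What to change.** Amend Section 9.2 and the Statistical analysis entry of the summary, and carry the wording into the SAP:

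1. Use the reasons recorded under Sections 7.2.3 and 7.3.2 to form three groups: fully compliant; non-compliant for reasons unrelated to an AE or QTcF; and stopped or not completed because of an AE or QTcF. Describe the third group on its own.
2. Base the compliant versus non-compliant comparison on AEs with onset after the scheduled third dose. Events are recorded by date, so state how those dated Day 3 are handled. Continue to report dosing-period AEs descriptively.
3. State that tablets re-administered after vomiting do not change the compliance ratio.

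The reason, the tablets not taken and the onset date are already on the patient chart, so the cost is wording and programming. The downside is fewer AEs in the comparison. In the main group the contact falls between Day 3 and Day 7, which leaves 0 to 4 days of solicited follow-up after the third dose. The result also depends on the reasons being recorded accurately, and it remains a descriptive, non-randomised contrast.

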#### **Additional analysis in the sub-set population**

QTc data will be recorded and centrally analysed according to the method described in the ICH guideline E14. The impact of all recorded covariates on QTc prolongation will be investigated through analysis of covariance techniques.

For the AESIs possibly related to cardio-toxicity, a correlation analysis with QTc values recorded at the visit of Day 3 (both before and 3-4 hour after treatment administration) will be carried-out. Occurrence of these events will also be studied with respect to distance from food intake.

Laboratory values will be analysed after normalization. Shift tables from normal to abnormal and vice-versa will be generated.

All the analyses previously described will be also performed by class of age and by type of Plasmodium.

### **9.3 Determination of sample size**

According to the cases registered in the previous years in the area where the study is performed, it should be possible to include approximately 10,000 cases of malaria confirmed by a parasitological diagnosis or diagnosed according to WHO criteria. This number of cases will allow identification of “rare” adverse events (incidence: 1 case/3,000 patients) with a 95% probability.

The sample size computation for the nested study (~1,000 patients) has been also based on feasibility considerations. The focus of this sub-set study will be on the combination of AESIs related to cardio-toxicity/prolonged QT (see above). In this sub-set, there will be a probability of 0.95 (0.865) of observing at least one cardiac AESI assuming that the true incidence of this event is 0.003 (0.002). For such a sample size, if no events have been observed, the upper limit of the 95% confidence interval for the probability of such event is 0.003.

## **10. DATA MANAGEMENT**

### **10.1 Collection and validation of data**

At the inclusion of a patient in the study, the data will be collected on **study specific logs and CRFs**. These forms will report the initials of the patient’s name/middle/surname, the patient ID number and a code shall allow the identification of the people (HF Study team and CHA) who have recorded the information in the patient chart.

At least twice a week, patient charts will be provided by HF study team to the CHA of the concerned villages (depending on the available human resources in the designated study health; conversely, CHA can regularly pick up the charts in the health facilities) in order to allow the CHA to perform the patient’s follow-up contact at Day 5 ( $\pm 2$  days).

As per the agreed monitoring schedule, the study monitor shall perform additional monitoring visit as necessary to verify completeness of such forms, to verify the registries of the patients with at least 28 days of follow-up from the enclosure in the study.

There will be 100% source data verification of all informed consent forms, AE and SAE recordings by the study monitor during monitoring visits of the 1,000 cohort and 5% of the 9,000 cohort and if there is more than 10% errors in the 5% then 100% review will be done.

Patient's forms will be transferred to the site Principal Investigator (PI) or designee at the HDSS. Form review meetings will be organised regularly, during which the PI, his/her team and the people responsible for the pharmacovigilance in the countries participating in the study shall determine the causal relationship between any of the recorded adverse event and the investigational product. This relationship shall be recorded on the patient form. These forms will be also reviewed by the study team to verify their completeness. One of the three copies of these charts shall subsequently be transmitted for data-entry and then entered into the local database, while the original chart shall be sent to the sponsor and the third copy of the chart shall be kept by the responsible persons for pharmacovigilance in the countries participating in the study.

Once the data is entered, verified and cleaned it will be uploaded into the central database based at Accra.

The sponsor study coordinator shall organise in a regular fashion the capture of these data by each HDSS together with the results of the thick blood smears of those patients.

Queries on the entered data will be generated by the central data manager based in Accra and periodically sent to the HDSS centres for resolution. The concerned HF and HDSS team shall have to answer by confirming or amending the initial data on the specific query form. A copy of the answered query form will be attached to the local copies of the patient chart. The returned answered query will be attached at the original copy of the patient chart stored by the sponsor.

After data capture, the adverse events shall be classified by MedDRA system organ class, preferred term.

The central database and original patient charts will be stored by the Sponsor in Accra, Ghana.

### **10.2 Quality control of data on site**

Approximately 10% of the forms collected in each health facility shall be verified against the centre's registries and charts.

In case specific problems are encountered in a centre, the percentage of charts verified shall be increased and corrective actions shall be implemented.

The quality control shall be undertaken by a qualified monitor, assigned by the sponsor.

### **10.3 Quality control of the preparation of thick blood smear slides**

The sample preparation technique will be quality controlled by one of the trainers. This person shall visit each site during the course of the study to verify the microscopic slides.

These visits shall be frequent at the start of the study, then may become decreasingly frequent if the quality of the samples is satisfactory. In case anomalies are detected during these study visits, or during the examination of the samples, the concerned Health Agent shall receive additional training.

A provisional schedule or calendar of supervision visits shall be initiated at the end of the training phase.

#### **10.4 Quality control of thick blood smear sample reading**

10% of the microscopic slides shall be quality controlled by a second qualified microscopist, who is independent from the centre where the initial microscopy took place. The procedures for quality control will be detailed in an ad hoc specification protocol.

#### **10.5 Data-entry**

The data entry will be performed at the HDSS centres by trained teams. The sponsor will develop the source documents and CRF templates and database that will be used for data capture and data entry. The source documents will be completed by the study teams at the health facilities where the patients are seen and followed up. A schedule will be developed at every centre for the transmission of completed forms to the HDSS PI. The completeness of all forms will be verified at the health facilities by internal quality control checks before being logged out and sent to the HDSS. Upon receipt at the HDSS all forms will be logged in and verified for completeness, consistency and legibility. The forms will then be accepted and handed over to the data entry personnel for data entry.

In case of need, queries will be sent via email to the health facility and HDSS teams for resolution of the questions and then returned back to the data entry centre. The data will be entered, verified and cleaned. All the data will be backed up and archived daily. A 100 % QC check of the data base with the forms will be performed by site study team. Once the data set is verified by the data manager and deemed cleaned it will be archived and transferred monthly to the central database in Accra by the data manager.

#### **10.6 Data cleaning and data base locking**

Monthly data base locks will be implemented across all HDSS. Data contained in the monthly locked database will be transferred to the central database in Accra and no alterations of such data can be performed afterwards by the HDSS. At the end of the study the centrally aggregated data, will be verified by the sponsor team in collaboration with Sigma-Tau. Once declared clean, the database will be locked before data analysis is performed.

A copy of the data base will be provided to Sigma-Tau for the additional Regulatory analysis.

